## Abstract

**Background:**

Epidural analgesia during labor can provide effective pain relief, but can also lead to adverse effects. The practice of moderate exercise during pregnancy is associated with an increased level of endorphins in the blood, and this could also provide pain relief during labor. Aerobic water exercises, rather than other forms of exercise, do not negatively impact articulations, reduce edema, blood pressure, and back pain, and increase diuresis. We propose a randomized controlled trial (RCT) to evaluate the effectiveness and safety of a moderate water exercise program during pregnancy on the need for epidural analgesia during labor.

**Methods:**

A multi-center, parallel, randomized, evaluator blinded, controlled trial in a primary care setting. We will randomised 320 pregnant women (14 to 20 weeks gestation) who have low risk of complications to a moderate water exercise program or usual care.

**Discussion:**

The findings of this research will contribute toward understanding of the effects of a physical exercise program on pain and the need for analgesia during labor.

**Trial registration:**

ISRCTN Registry identifier:14097513 register on 04 September 2017. Retrospectively registered.

## Background

Epidural analgesia is one of the most effective methods for reducing labor pain [1–3]. This technique is used for pain relief in labor in 25% of women in the United Kingdom [4], 58% of women in the United States, [5] and 58 to 61% of women in Spain [6, 7].

Although epidural analgesia provides effective pain relief, it may lead to complications or adverse effects, with maternal and fetal morbidities. The risk of accidental dural puncture due to epidural catheter insertion is 1.5%, and approximately half of these cases have postdural puncture headache [8–10]. There are many other complications related to epidural analgesia and these including: high block, which can lead to maternal hypotension, respiratory arrest, and loss of consciousness; epidural hematoma, a serious complication that can cause compression or ischemia of the spinal cord and subsequent paralysis; and local anesthetic toxicity due to an inadvertent intravascular injection that provokes respiratory and cardiac arrest [11].

In addition, some studies reported an association between epidural use and prolonged labor, increased use of instrumental deliveries, increased use of Caesarean sections, [11–13] and increased utilization of hospital resources [14]. Many caregivers are currently searching for non-pharmacological methods to control pain during labor, [15–18] and a major report from the World Health Organization has encouraged this approach [19]. Non-pharmacologic approaches to pain management include a wide variety of techniques that aim to reduce the physical sensations of pain and to prevent suffering by addressing the psychoemotional and spiritual components of care. Some studies suggest that exercise increases beta-endorphin levels, provides pain relief during labor, and reduces the need for epidural analgesia [20–23]. However the results of studies on reduced pain perception [24] due to increased levels of beta-endorphins at the time of delivery are inconclusive [24, 25].

Clinical practice guidelines (CPG) and national and regional strategies recommend exercise during pregnancy because it provides beneficial effects without adversely affecting the fetus. In particular, the American College of Obstetricians and Gynecologists (ACOG) guidelines from 2002 [26] and 2015 [27] and the Canadian Society of Gynecology and Obstetrics (SOGC) guidelines from 2003 [28] recommend exercise during pregnancy and the postpartum period. These guidelines suggest a minimum of 30 min of moderate daily exercise (about 150 min per week) for healthy pregnant women without obstetric complications. This exercise regimen can improve the health of active or sedentary women, with no risk to the fetus [29, 30].

Some observational studies reported that performance of exercise may help prevent and treat gestational diabetes and pre-eclampsia during pregnancy [31–33], and reduce the rates of Cesarean section, instrumental delivery, and postpartum recovery time. However, randomized clinical trials provided only limited support for these benefits [27].

Aerobic activity during pregnancy does not negatively impact preterm birth, newbornweight, but is related to a minor maternal weight gain [29, 34]. However, physical inactivity and excessive maternal weight are recognized risk factors for development of complications, such as gestational diabetes and maternal obesity [27]. A large cohort study of the relationship between exercise and pregnancy loss reported increased abortion in women performing aerobic high-impact exercise (jogging, ball games, and racquet sports) for more than 7 h per week, but no association between exercise and the risk of miscarriage after 18 weeks of gestation [35].

Aquatic-aerobic exercise has some advantages over other forms of exercise. These include reduced impact on articulations, less edema, increased diuresis, reduced arterial pressure, better control of body weight, less back pain, better temperature control, and lower probability of miscarriage [36]. Moreover, aquatic-aerobic exercise is not associated with risk of urinary or vaginal infections [27, 37–39]. Also, because aquatic-aerobic exercise is a group activity, compliance should be greater and there will be emotional interactions among women, and this may motivate the participants to develop healthier behaviors outside of exercise class [40, 41]. Moreover, aerobic water exercise could be an alternative to pain control during labor, reduce adverse effects such as dystocia, increase maternal satisfaction, and is likely to be readily accepted by pregnant women.

We propose a randomized clinical trial to analyze the effectiveness, safety, and cost of a moderate aerobic water exercise program on the use of epidural analgesia during labor.

### Objectives

The main objective of this study of women with uncomplicated pregnancies is to compare a standard antenatal care program with a program of aquatic-aerobic exercises of moderate intensity on the use of epidural analgesia during labor. The secondary objectives are to test the effect of the water exercise program on use of epidural analgesia before 6-cm cervical dilation, dystocic delivery, induction of labor, subjective satisfaction with the experience of childbirth, pain perception during the first stage of labor, duration of labor (first and second stages), and postpartum depression, and to assess the safety and cost-effectiveness of the aquatic-aerobic exercise program.

## Methods/design

We designed a multi-center, parallel, randomized, evaluator-blinded, controlled clinical trial of 320 pregnant patients from primary care centers in Mallorca, Spain. Participants will be randomly allocated to a moderate aquatic-aerobic exercise group or a usual antenatal care group. Figure 1 summarizes the study design and timeline. Participants will be monitored from recruitment (at 14 to 20 weeks gestation) until the end of pregnancy, and then followed for 1 month after birth.

**Fig. 1 Fig1:**
[figure not shown]
Study design and timeline

### Study population

Women will be recruited from 5 primary care centers in Mallorca, Spain. The participating primary care centers are all in a health district of a tertiary obstetric metropolitan hospital which has facilities for deliveries at 28 weeks or more. Women who are willing and able to comply with the requirements of the study will be invited to participate. Gestational age will be determined by the last menstrual period and/or by early ultrasound.

#### Inclusion criteria

Pregnant women, who are 18 and 40 years-old and pregnant for 14 to 20 weeks.Pregnancy at low risk of complications (i.e. all women have singleton pregnancies, and none have medical, obstetric, or psychiatric problems).

#### Exclusion criteria

Severe and poorly controlled hypertension, type 1 diabetes, or asthma.Hemodynamically significant heart disease, recent episode of deep venous thrombosis, hepatic insufficiency, or renal failure.Diagnosed mental illness or contraindications for physical activity.Multiparity (≥6 pregnancies), recurrent spontaneous miscarriages (≥3), incompetent cervix, increased risk of premature labor, persistent second or third trimester bleeding, uncontrolled gestational diabetes, severe isoimmunization, or planned Caesarean section.Severe anemia (hemoglobin < 9 mg/dL), recurrent urinary tract or vaginal infection, BMI above 35 or below 17, active and heavy smoker (> 20 cigarettes/day), any drug use or abuse, chronic infectious disease (HIV, hepatitis B, hepatitis C).Not being able to swim, communication difficulties, or unwillingness to provide informed consent.

### Sample size

The sample size calculation is based on the primary outcome measure and the primary analysis for the intention-to-treat population. Obstetric epidural analgesia in vaginal deliveries is estimated as 61% [42, 43]. Thus, we estimate a total reduction of at least 20% in the use of obstetric epidural analgesia in the intervention group based on a secondary analysis of a previous randomized clinical trial [21]. We adjusted the sample size for an estimated follow-up loss of 15% and a 0.05 two-sided level of significance (α = 5%).

Women in the control group might decide to attend other facilities to practice water exercise, swimming, or other physical activities. Thus, we increased the sample size by 15% to account for increased performance of exercise by women in the usual care group, so the final sample size will be 160 for each group (320 women total).

### Procedures, recruitment, randomization, and collection of baseline data

Each participating primary care center will have at least one midwife from the research team invite potential candidates to participate in the clinical trial and perform all procedures. Willing participants who meet the eligibility criteria will be enrolled after reading and signing an informed consent agreement. Then, entry details will be recorded on a trial entry form, and they will be randomized to the aquatic-aerobic exercise group or the usual antenatal care group. The 1:1 randomization will be performed by a researcher not involved with treatment allocation, and will be in balanced blocks of six.

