### Blinding

The nature of this study did not allow blinding of women and midwifes to group allocation. However, the outcome assessments will be conducted by external personnel (not involved in the study) who will be blinded to allocation. To avoid a potential Hawthorne effect, in which women in the intervention group change their behaviors (e.g. avoid use of epidural analgesia) because they know they are being observed, the women were not specifically informed that use of epidural analgesia was the main outcome measure, although they were completely informed of all the aims of the study. The statistician and data entry staff were also blinded to allocations.

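### A single fixed block size of six, with unblinded midwives recruiting, could let some upcoming assignments be worked out if blocks run within centre or assignments are shared

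*Protocol article*

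**What the plan says.** The protocol article's section on procedures, recruitment and randomization fixes one block size: the randomization "will be in balanced blocks of six". No other restriction on the sequence is described.

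The same section gives recruitment to the research midwives. Each centre has "at least one midwife from the research team invite potential candidates to participate in the clinical trial and perform all procedures". The section on the study population puts the number of centres at five.

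The *Blinding* section states: "The nature of this study did not allow blinding of women and midwifes to group allocation". The people who recruit therefore also see the assignments made so far, at least at their own centre.

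Two safeguards are stated. Consent comes first: "Willing participants who meet the eligibility criteria will be enrolled after reading and signing an informed consent agreement". The trial entry form follows, and then randomization. The list is also handled independently: "The 1:1 randomization will be performed by a researcher not involved with treatment allocation".

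The article does not say whether blocks run within centre or across all centres, or whether the midwives know the block size.

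**The concern.** In a balanced block of known size, the assignments already made narrow down those still to come. Once three of six have gone to one arm, the rest of the block is settled. A recruiter who counts can then know the next assignment before deciding whom to invite, or when.

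This matters here because the primary outcome, epidural use in labor, depends partly on what the woman wants. The *Baseline data collection* section lists preference for analgesia among the items recorded at entry, so a likely predictor of the outcome is within the recruiter's reach. The study population section also leaves some judgement at entry, since women are invited if they appear able and willing to follow the study requirements. If women inclined to avoid an epidural were invited more readily when the exercise arm was due, the arms would differ before treatment began. Blinded outcome review and intention-to-treat analysis both act after enrolment and would not undo that.

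**Working it through.** The article gives no figure for predictability, so there is none to reproduce.

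**Inputs from the article.** Block of six at 1:1, so three per arm; 320 women; five centres. **Assumptions.** For the first two calculations, the recruiter knows the block size and every earlier assignment on her list. Centres are of equal size, 320 / 5 = 64 women each.

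**1. One full block of six.** There are C(6,3) = 20 equally likely blocks. An assignment is certain when one arm already has its three. The best guess is always the arm that lags; at a tie it is right half the time.

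| Position in block | Probability that it is certain | Probability that best guess is right |
|---|---|---|
| 1 | 0 | 0.5 |
| 2 | 0 | 0.6 |
| 3 | 0 | 0.6 |
| 4 | 2/20 = 0.1 | 0.7 |
| 5 | 8/20 = 0.4 | 0.7 |
| 6 | 1 | 1.0 |
| Sum | 1.5 | 4.1 |

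- Certain: 1.5 / 6 = 25%, or 0.25 × 320 = 80 women.
- Best guess right: 4.1 / 6 = 68.3%, against 50% by chance.

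Closed forms agree. With m = 3 per arm, the expected number certain is 2m / (m + 1) = 6 / 4 = 1.5. The expected number of correct guesses is m + 2^(2m−1) / C(2m, m) − 0.5 = 3 + 32/20 − 0.5 = 4.1.

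**2. One list of 64 per centre.** This is ten full blocks and the first four places of an eleventh.

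- Certain: (10 × 1.5 + 0.1) / 64 = 15.1 / 64 = 23.6%.
- Best guess right: (10 × 4.1 + 2.4) / 64 = 43.4 / 64 = 67.8%.

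**3. One central list over five centres, each midwife seeing only her own.** Simulation (2000 lists of 320, each woman assigned to a centre at random, guess made against the centre's own running imbalance) gives 51.0% correct, close to chance.

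**4. Randomly varied block sizes, lists of 64.** Simulation (2000 runs) with a recruiter who knows the set of possible sizes but not the size of the current block:

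| Block sizes | Certain | Best guess right |
|---|---|---|
| 6 only | 23.6% | 67.8% |
| 4, 6, 8 | 2.3% | 67.8% |
| 2, 4, 6 | 4.0% | 70.1% |
| 4, 6 | 5.5% | 69.1% |

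Varying the size removes most of the certainty. It does not reduce the advantage of guessing the lagging arm.

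**The case against.** The strongest objection is that predictability needs either a list per centre or midwives who pool their assignments, and the article describes neither. With one unshared central list the risk almost vanishes. This stands, and the point is conditional on it. A reader might infer from the text that midwives can work out the coming assignments throughout. The article does not support that: even in the unfavourable case only about a quarter are certain, and in the favourable case practically nothing can be inferred.

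It is also fair to say that consent and the entry form already precede randomization, and that someone independent runs it. Both deserve credit. They prevent an assignment from being changed for a woman already enrolled, but they do not govern whom a midwife approaches next.

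Concealment details may be in the full protocol, and their absence from an article is no fault. Publishing the block size does not show that the midwives were told it. What remains is what the article does fix: one constant block size, with unblinded recruiters.

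A reader might also conclude that selection of this kind would be beyond repair. That goes too far. Preference for analgesia is recorded at entry, and the *Statistical analysis* section allows logistic regression adjustment for confounders, so imbalance in that variable can be seen and adjusted for. Selection on unrecorded traits cannot.

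Finally, it is tempting to state a bias in percentage points of epidural use. That would be the preference imbalance between arms multiplied by the difference in epidural use between women with different preferences. The article gives neither, so no such figure is claimed.

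**Conclusion.** The point holds in conditional form. A constant block of six is an avoidable weakness when those who recruit can see past assignments. If blocks run within centre or assignments are shared, and the block size is known or inferred, about 25% of assignments are certain in advance (23.6% for lists of 64) and about 68% can be guessed. With one central list and no sharing, guessing is right about 51% of the time. The article does not settle which case applies.

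These figures describe opportunity. They do not show that selection happened, or how far it would move the primary result. The change is still worth making because it costs almost nothing and selection at enrolment is hard to correct afterwards.

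**What to change.** For all remaining enrolments, replace the fixed block of six with randomly varied sizes, for example 4, 6 and 8, and keep both the sizes and the list from the recruiting midwives. State whether the list is central or by centre. Keep the present order of consent, entry form and then randomization.

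If a single central list is in use, do not introduce stratification by centre as part of this change. It would create the separate lists that make guessing possible, and could raise the correct-guess rate from about 51% to about 68%. If lists already run by centre, varied sizes cut certain assignments to about 2% but leave the best guess near 68%, which is why withholding the sizes and list is also needed.

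Compare baseline preference for analgesia by arm, using the value recorded before the assignment was known, and name it as a covariate in the adjusted logistic model. This can be done even if enrolment is complete.

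The cost is a new computer-generated list and arm totals that may differ by a few women. Exact equality is not assured now either, since 320 / 6 = 53.3 blocks.

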### Intervention

The women randomized to the water aerobics group will participate in 45 min water aerobics classes held three times weekly in an indoor pool (28–30 °C) for 5 months. This procedure is based on recommendations of the American College of Sports Medicine [36], which proposes 3–5 classes per week, a training zone of 55–65% of maximum heart rate, classes of 20–60 min duration, maximum heart rate of 140 bpm, and maintenance of body temperature below 38 °C.

### Aquatic exercise

Four sets of exercise were developed for the study, each set of exercise include exercises that looks at the full work of muscle groups and include breathing and relaxation techniques. All exercises will be performed with coordinating breathing:Warm-up out of water (5 to 7 min).Warm-up in water (5 to 10 min).Moderate aquatic exercise (20 min).Breathing and relaxation exercises (5 min).Playful exercises (5 min).

The intervention will stop if any of the followings events appear during the trial: metrorrhagia, placenta previa, premature rupture of membranes, intrauterine growth retardation, severe anemia, or any contraindications to being physically active [27].

Women in the control group will receive standard antenatal care, and the customary information given by a midwife or general practitioner. They were not discouraged from exercising on their own.

### Follow up of women and infants

Midwifes will be responsible for data collection from the clinical history and from the questionnaires in all follow-up visits at gestation times of 17, 27, and 37 weeks. One month after birth, a follow-up visit will be used to assess maternal well-being, satisfaction with care, use of breast feeding, and early infant complications. Resource utilization and delivery of information regarding birth and infant outcomes will be obtained from the woman’s and infant’s case notes by the local research coordinator.

### Measurement of outcomes

#### Main outcome variables

The main outcome measure will be the incidence of epidural analgesia use during labor. This will be determined through review of the clinical history by a member of the research team who is blinded to the allocations.

#### Secondary outcome variables

##### Maternal medical outcomes

Incidence of epidural analgesia use of epidural analgesia before 6-cm cervical dilationMethod of delivery (normal spontaneous vaginal, assisted vaginal, or Caesarean section).Episiotomy or perineal tear.Morbidity: major complications (during the antepartum, intrapartum, and postpartum periods), poor labor progress, intrapartum maternal fever, type of membrane rupture.Pregnancy weight gain.Induction of labor.Robson group, cervical dilation, time of active labor, time of expulsive labor.

### Total labor pain

Total labor pain will be measured using a visual analogue scale (VAS). The VAS is one of the most used pain assessment instruments in research and clinical practice. Previous research indicted the VAS is reliable and sensitive for assessment of labor pain [44].

### Edinburgh postnatal depression scale (EPDS)

The EPDS is a questionnaire originally developed to assist in identifying possible symptoms of depression in women during the postnatal period. It also has adequate sensitivity and specificity for identification of depressive symptoms in the antenatal period, and is useful in identifying symptoms of anxiety. The Spanish language version of the EPDS has been validated [45].

This study will also collect data on health resource utilization and pregnancy outcome, and will record and compare the rates of pregnancy complications and perinatal outcomes in the two groups. The latter will be obtained (with informed consent) from the existing computerized obstetric database and include:

### EuroQol five dimension questionnaire (EQ-5D)

The EQ-5D will be used to assess quality of life. This is a standard instrument used to measure overall health status, and its has good validity and reliability for individuals with various health conditions [46]. The EQ-5D is a preference-based HRQL measure with one question for each of the five dimensions that include mobility, self-care, usual activities, pain/discomfort, and anxiety/depression. The EQ-5D questionnaire also includes a Visual Analog Scale (VAS), by which respondents can report their perceived health status with a grade ranging from 0 (the worst possible health status) to 100 (the best possible health status).

#### Neonatal medical outcomes

Signs of intrapartum fetal distress (fetal heart rate abnormalities, birth weight, gestational age, Apgar score, pH, umbilical cord blood).

#### Resource utilization outcomes

Oxytocin/prostaglandin induction, oxytocin augmentation, amniotomy, narcotic analgesia, other type of pain relief (tub/bath/shower), antibiotic use, continuous electronic fetal monitor, need for maternal blood transfer, maternal length of stay (48 h vs. more than 48 h), admission to a neonatal intensive care unit, need for positive pressure ventilation, sepsis work-up and treatment, and neonatal readmission (< 28 days-old), non-delivery admissions and emergency room: antepartum hospital admission, emergency room without admission, postpartum maternal readmission (30 days post-partum), use of comprehensive perinatal services program, and non-planned visits to a primary care center.

